##### Fugl-Meyer Assessment—Upper Extremity Subscale

The FMA-UE measures motor function of the paretic upper limb (27, 28). A total of 33 items are assessed and each item is rated on a three-point ordinal scale (0 = cannot perform, 1 = performs partially, and 2 = performs fully). The sum score ranges from 0 to 66.

##### Action Research Arm Test

Upper limb capacity is measured with the ARAT and includes four categories: grasp (six items), grip (four items), pinch (six items), and gross movement (three items) (29–31). Each item is rated on a four-point ordinal scale (0 = no movement; 1 = the movement task is partially performed; 2 = the movement task is completed, but takes abnormally long; and 3 = the movement is performed normally), leading to a maximum overall score of 57 points.

##### EuroQol Five Dimensions Five Levels Questionnaire

The EQ-5D-5L is a self-completed questionnaire regarding health-related quality of life (32, 33). Each of the five assessed domains (mobility, self-care, usual activities, pain/discomfort, and anxiety/depression) is described by one out of five responses, ranging from “no problem/not at all” to “unable/major problem.” In addition, the patient is asked to rate his or her self-rated health on a Visual Analog Scale. Approval of the EuroQol Research Foundation to use the German (Switzerland) EQ-5D-5L paper version has been obtained (March 13, 2017).

##### Modified Rankin Scale

Global disability is assessed with the mRS, which includes an informal interview with the patient, to rate the extent of a patient’s post-stroke disability or impairment in ADLs on a six-point ordinal scale, ranging from 0 = “no symptoms at all” to 5 = “severe disability” (34–36).

##### Motor Activity Log—14 Item Version—Quality of Movement Subscale

The MAL—14 QOM measures the patient-reported quality of paretic upper limb use in daily life by performing a semi-structured interview (24–26). Analogue to the AOU subscale, 14 ADL tasks are questioned. Patients score how well the paretic upper limb helped during this activity on a six-point ordinal scale, with item scores ranging from 0 [my weaker arm was not used at all for that activity (not used)] to 5 [the ability to use my weaker arm for that activity was as good as before the stroke (normal)], and a total score ranging from 0 to 5.

##### Global Rating of Perceived Changes

With the GRPC, the patients rate their perceived changes in the daily life usage of the paretic upper limb, using the following seven-point Likert scale: score 1 is much better; score 2 = a little better, meaningful; score 3 = a little better, not meaningful; score 4 = about the same; score 5 = a little worse, not meaningful; score 6 = a little worse, meaningful; and score 7 = much worse (37).

##### Quantitative Sensor Data for Compliance and Activity Counts

Adherence will be monitored through the weekly reminder calls and through analysis of the gathered Quantitative Sensor Data and smartphone App usage data. The Quantitative Sensor Data measure the “Arm Activities” by using the acceleration data, aggregated over 1 min during wearing the activity tracker. This refers to Arm Activities of both the paretic and non-paretic side and allows comparing both changes in Arm Activities over time for each upper limb during the 6-week intervention, as well as comparing Arm Activities between the paretic and non-paretic upper limb.

##### Safety

Adverse Events will be gathered from inclusion upon follow-up. Assessments will be made during each study visit, as well as by the weekly phone calls during the intervention period. Each time, study subjects will be actively questioned by unblinded study personnel whether they experienced any AEs. In case of occurrence of a related AE, the time of onset, the duration, the resolution, actions that were taken, the intensity as well as the relationship with the study intervention will be recorded.

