
### Study Aim

The primary aim of this study is to determine the post-intervention and long-term effects of wearing a wrist-worn, commercially available tracking device that provides multimodal feedback for 6 weeks on patient-reported amount of paretic upper limb use in daily life in hemiparetic subjects beyond 3 months after stroke, when compared with a control group receiving an identical looking device providing no feedback. The secondary aims are to examine the compliance to use the device, and explore the effect on motor function of the paretic upper limb, upper limb capacity, patient-reported quality of paretic upper limb use in daily life, global disability, health-related quality of life, and during the 6-week intervention, the compliance and activity counts of the paretic and non-paretic upper limb. As a measure of safety, the incidence and severity of side effects related to the long-time wrist-worn feedback intervention during the study period will be investigated. Furthermore, the Minimal Clinical Important Difference (MCID) of the Amount of Use (AOU) subscale of the Motor Activity Log—14 Item Version (MAL—14) will be established.

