#### Control Intervention

Subjects in the control group will use the same devices in the same way as the intervention group. They will wear the “ARYS™ me|tracker” on their paretic and the “ARYS™ pro|tracker healthy” on their non-paretic wrist. The “ARYS™ me|tracker” will have a custom firmware installed that deactivates both the vibration module as well as the LED-progress bar. Therefore, subjects in the control group will neither receive nor know about any feedback happening in the intervention group. They will not receive a smartphone with the “ARYS™ me|app.” The one-to-one instruction for the control intervention takes up to 15 minutes. Analogue to the patients in the experimental group, they can consult the accompanying manual, ask questions during the weekly telephone calls, and, when needed, contact the hotline.

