### Statistical Analysis

Patient demographics and baseline data will be analyzed by trial arm using summary descriptive statistics. Baseline differences between groups will be tested by the independent-samples *t*-test for parametric data, Pearson’s χ^2^ test for categorical data, and the Mann–Whitney *U* test for non-parametric data.

Differences in change scores (T0–T1) between groups will be analyzed for the primary outcome (MAL—14 AOU) and secondary outcomes (MAL—14 QOM, FMA—UE, ARAT, EQ-5D-5L, mRS, and Quantitative Sensor Data). In addition, change will be monitored in the follow-up assessments (T1–T2). An analysis of covariance will be applied, with the baseline value of the measure of interest as a covariate. Compliance to using the devices during the 6-week intervention period and safety data will be presented by trial arm with descriptive statistics and compared between groups by the independent-samples *t*-test, Pearson’s χ^2^ test, or Mann–Whitney *U* test, depending on the nature of the data distribution. In a secondary analysis, compliance to wearing the trackers—based on the Quantitative Sensor Data—will be added as a covariate for analysis of the primary outcome MAL-14 AOU.

All randomized subjects will be included in the analyses according to the intention-to-treat approach. Missing data will be imputed. In addition, differences in baseline characteristics of patients who did and did not dropout will be formally tested. A *p*-value of <0.05 will be considered to be statistically significant. The analyses will be performed in IBM SPSS Statistics 23.

Furthermore, the compliance to the intervention will be presented with descriptive statistics. The MCID will be calculated based on the MAL—14 AOU and GRPC scores, analogue to previous work by Lang et al. (37).

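### Adverse-event details are recorded only for events already considered related, so the comparison of related events and their severity could depend on the arm

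*Protocol article*

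**What the plan says.** Collection starts broadly. The Safety section under Secondary Outcomes states that "Adverse Events will be gathered from inclusion upon follow-up", and that at each visit and weekly call "study subjects will be actively questioned by unblinded study personnel whether they experienced any AEs". Table 1 lists adverse events without restriction at baseline, during the intervention and at both later assessments.

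The recording rule is narrower. The same section continues: "In case of occurrence of a related AE, the time of onset, the duration, the resolution, actions that were taken", and the sentence ends by adding that "the intensity as well as the relationship with the study intervention will be recorded".

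The Study Aim section defines the safety measure through relatedness: "the incidence and severity of side effects related to the long-time wrist-worn feedback intervention during the study period will be investigated". The Statistical Analysis section then plans that "safety data will be presented by trial arm with descriptive statistics and compared between groups", using a t-test, χ² test or Mann–Whitney test according to the data. It does not say whether this means all events or related events.

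**The concern.** Relationship appears in the recording rule twice: as the condition for opening the record, and as one of the items recorded once it is open. Read as written, someone must settle relatedness before there is a structured description to settle it from. An event set aside as unrelated has no planned onset, duration, intensity, outcome or stated reason.

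This touches the safety measure that the trial declares, because the incidence and severity of related side effects are exactly what passes through the condition. The arms are also not symmetrical in what an event can be attributed to. The control tracker has "custom firmware installed that deactivates both the vibration module as well as the LED-progress bar". A control complaint can hardly be put down to feedback that the device does not give, while the same complaint in the experimental arm can. The opposite error is possible too. The intervention aims at more arm use, and arm pain from that use might be considered unrelated to a wristband, in which case its intensity and timing would not be recorded. At stake is whether a difference, or the absence of one, in related events and severity can be read as an effect of the device.

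**Working it through.** **Sections side by side**

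| Step | Where stated | All AEs or related only |
|---|---|---|
| Participants are asked | Safety | all |
| Events are gathered | Safety; Table 1 | all |
| Onset, duration, resolution, actions, intensity, relationship | Safety | related only |
| Declared safety measure | Study Aim | related only |
| Between-arm comparison | Statistical Analysis | not specified |

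A count of all events by arm therefore need not pass through the relatedness condition. Severity, timing and the related-event count do.

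**Can such a condition distort a comparison?** The article gives no figure for the safety comparison, so there is none to reproduce. It gives no AE rate and no probability of being judged related. The inputs below, apart from the arm size, are assumptions.

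- Arm size: 62 randomised 1:1, so 62 / 2 = 31 per arm; no dropout is applied.
- True risk p that a participant has an AE: equal in both arms, 20%, 30% or 40%.
- Probability that the event is judged related: q_E in the experimental arm, q_C in the control arm.

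The number of participants with a recorded related event is then binomial with n = 31 and risk p × q_E or p × q_C. For p = 0.20, q_E = 0.7 and q_C = 0.3, the expected counts are 31 × 0.20 × 0.7 = 4.3 and 31 × 0.20 × 0.3 = 1.9. The rejection rate is the sum of the exact probabilities of all 2 × 2 tables with two-sided p < 0.05.

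| q_E / q_C | χ² (uncorrected), p = 20 / 30 / 40% | Fisher exact, p = 20 / 30 / 40% |
|---|---|---|
| All AEs, no condition | 0.050 / 0.050 / 0.052 | 0.023 / 0.027 / 0.028 |
| 0.5 / 0.5 | 0.055 / 0.053 / 0.050 | 0.010 / 0.018 / 0.023 |
| 0.7 / 0.3 | 0.191 / 0.268 / 0.351 | 0.062 / 0.148 / 0.244 |
| 0.9 / 0.3 | 0.325 / 0.466 / 0.620 | 0.154 / 0.331 / 0.509 |

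The true risk is equal throughout, so every rejection is false. If judgement does not differ by arm, the condition leaves the error rate near 5%. If it does differ, the related-event comparison can be misled while the all-AE comparison is not. The table shows what the mechanism can do. It does not show that differential judgement will occur.

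**The case against.** Several points on the other side stand.

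- **Who judges.** A reader might infer that unblinded staff decide relatedness. The article names unblinded staff as those who ask the questions; it does not say who judges, or whether that person knows the arm.
- **All events.** A reader might infer that there will be no all-event denominator and that an excess of unrelated events would be invisible. The text does not support this. Events of any kind are asked about and gathered, the Data Collection section seeks AEs even after a participant stops the intervention, source data stay at the sites, monitors can see patient files, and the trial management committee reviews safety monthly. What lacks a plan is the structured detail on events considered unrelated.
- **An extreme example.** Four events in each arm, with all four experimental and no control events called related, would turn 4/31 versus 4/31 (p = 1.0) into 4/31 versus 0/31. Pearson's χ² then gives p = 0.039. But this assumes the most extreme split, two expected cells are only 4 × 31 / 62 = 2, Fisher's test gives p = 0.113, and χ² is only one of three tests listed. It is no estimate of the likely effect.
- **Unblinded questioning.** This is not a fault. Talk of vibration or lights would reveal the arm, so keeping it away from the outcome assessors protects the primary outcome.
- **Low stakes.** The devices are CE-marked Class 1, the trial was approved as minimal risk, and safety is a secondary outcome for which the trial is not powered.

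One point stands only in part. The wording may be loose: a relationship field would be largely redundant if every recorded event were already related, and the full protocol and case report forms are not shown. But the article does not merely leave the rule out. It states one, and as stated the rule makes relatedness the condition for the record.

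**Conclusion.** The point holds in a limited form. As written, relatedness is decided before the field that documents it, and events considered unrelated have no planned severity, timing or causality record. Because the declared measure is related side effects and their severity, because unblinded staff elicit events, and because only one arm receives feedback, that part of the between-arm comparison could depend on the arm.

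The documents do not show that the safety comparison as a whole is biased, and they give nothing from which to size a bias or fix its direction. The false rejection rates of 19 to 35% (χ²) and 6 to 24% (Fisher) at 0.7 versus 0.3 rest entirely on assumed event risks and attribution probabilities. The point is worth correcting because the correction is cheap. It has no bearing on the primary analysis.

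**What to change.** Two changes:

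1. In the Safety section, record onset, duration, intensity, actions, outcome and relationship for every AE in both arms. Relationship becomes a field on the form, not the condition for completing it.
2. In the Statistical Analysis section, compare all AEs (incidence and severity) by arm first, and related AEs second.

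Unblinded questioning can stay as it is, and masked review of relatedness is not needed for this correction. The cost is a changed completion rule for the electronic case report form and a small added documentation load at visits and weekly calls that already ask about AEs.

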#### Descriptive Measures

Next to the above described outcome measures, the following data will be collected at baseline to characterize our cohort: demographic data, stroke event data, comorbidities, handedness [Edinburgh Handedness Inventory (38)], neglect [Apples Test (39)], social situation, and neurological functions [National Institutes of Health Stroke Scale (40)].

### Data Collection

Assessments will take place at one of the participating centers, or at the patients’ home when he or she is not able to visit one of the study centers. All assessors will be trained prior to the first screening during which they will receive proper instruction and guidance regarding all outcome parameters and assessments that will be taken. The trial management committee (TMC) will be available for questions.

In the case that a patient discontinues or deviates from the intervention protocol, all efforts will be made to obtain at least the primary outcome measure (MAL—14 AOU) and the safety measures (AEs) at the pre-defined study visits. All patients will receive a reminder for each visit to diminish retention and incomplete follow-up.

### Data Management

Study data will be recorded in electronic Case Report Forms (eCRF). For each enrolled study participant, an eCRF will be maintained. These eCRFs will be kept current to reflect subject status at each phase during the course of study. The participants’ code will be assigned in a random order. Source data will be available at the respective study site to document the existence of the study participants. Source data will include the original documents relating to the study, as well as the medical treatment and medical history of the participant. All study data will be archived for a minimum of 10 years after study termination or pre-mature termination of the clinical trial in a secure database. Study data will be managed using REDCap™, being hosted on servers administered by the Data Informatics Services Core of cereneo Schweiz AG. To access the REDCap™ site, all study team users of the REDCap™ system will be issued a unique username and password that is generated and maintained by our administrator on the REDCap™ server.

The study data will be analyzed by the TMC after study completion (last patient, last visit). No interim analysis will be performed. Only the study coordinators and principle investigators will have access to the final trial dataset.

### Statistical Analysis

Patient demographics and baseline data will be analyzed by trial arm using summary descriptive statistics. Baseline differences between groups will be tested by the independent-samples *t*-test for parametric data, Pearson’s χ^2^ test for categorical data, and the Mann–Whitney *U* test for non-parametric data.

Differences in change scores (T0–T1) between groups will be analyzed for the primary outcome (MAL—14 AOU) and secondary outcomes (MAL—14 QOM, FMA—UE, ARAT, EQ-5D-5L, mRS, and Quantitative Sensor Data). In addition, change will be monitored in the follow-up assessments (T1–T2). An analysis of covariance will be applied, with the baseline value of the measure of interest as a covariate. Compliance to using the devices during the 6-week intervention period and safety data will be presented by trial arm with descriptive statistics and compared between groups by the independent-samples *t*-test, Pearson’s χ^2^ test, or Mann–Whitney *U* test, depending on the nature of the data distribution. In a secondary analysis, compliance to wearing the trackers—based on the Quantitative Sensor Data—will be added as a covariate for analysis of the primary outcome MAL-14 AOU.

All randomized subjects will be included in the analyses according to the intention-to-treat approach. Missing data will be imputed. In addition, differences in baseline characteristics of patients who did and did not dropout will be formally tested. A *p*-value of <0.05 will be considered to be statistically significant. The analyses will be performed in IBM SPSS Statistics 23.

Furthermore, the compliance to the intervention will be presented with descriptive statistics. The MCID will be calculated based on the MAL—14 AOU and GRPC scores, analogue to previous work by Lang et al. (37).

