### Stepwise Procedures

Subjects will be recruited at three study centers in Switzerland: University Hospital Zurich (academic hospital), cereneo—Center for Neurology and Rehabilitation (rehabilitation clinic), and Zürcher RehaZentrum Wald (rehabilitation clinic) by the local principal or sub-investigator. The participant timeline is displayed in Figure 1. The written participant information and informed consent forms (in German) can be obtained by the corresponding author. After having obtained participant consent, the baseline assessment (T0) will be performed. Randomization will take place after the baseline assessment and depending on the group allocation, participants will be handed over the trial arm-specific devices and receive instructions accordingly. Randomization and device hand-over will be performed by study personnel not involved in assessments (e.g., physical therapist and study nurse). The intervention period has a total duration of 6 weeks. The post-intervention assessment (T1) takes place at day 45 ± 3 after baseline and the follow-up assessment (T2) at day 90 ± 6 after baseline.

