#### Experimental Intervention

Participants in the experimental group will wear an “ARYS™ me|tracker” on the paretic wrist and an “ARYS™ pro|tracker healthy” on the non-paretic wrist (see Figure 2). The trackers are hardware-wise identical and consist of: the actual tracker (silver with a feedback and communication module for the paretic side, which is deactivated for the control group); a reference tracker (black-brown tracker for the non-paretic side); and an exchangeable, flexible black wristband. Both elements are made out of biocompatible materials. The devices should be worn every day, as long as possible over a period of 6 weeks. During this 6-week period, a three-axis accelerometer in each device will constantly monitor the subjects’ arm movements. A threshold of 0.1 g acceleration is defined for detection of movements. This raw acceleration data, aggregated over 1 min, will be converted on-device in so-called “Arm Activities.” Starting from a pre-defined goal-value, new daily goals will be automatically calculated every day from the rolling average of the last 30 days plus 3% (e.g., after the first intervention week, patient X shows an average number of 100 “Arm Activities” per day. For day 8, his daily goal therefore becomes 103 “Arm Activities”). Patients will constantly be challenged to slightly increase their Arm Activities without ever being overstrained. Assuming a steady arm activity during the course of the day, a linear target activity line will be calculated (default start/end times: 8:00 a.m. to 10:00 p.m.). The already reached “Arm Activities” will be compared with an intermediate target value. After 30 min of inactivity, the “ARYS™ me|tracker” vibration engine will provide the subject on the paretic wrist with two short double pulses and up to four LEDs will light up in orange color to remind to make more use of this arm (Level 1 Reminder). If 30 min later, “Arm Activities” are still below the intermediate target, a second escalation level of the reminder is triggered: five long vibrating pulses will be provided and up till four LEDs will light up in red color (Level 2 Reminder). Thereafter, the escalation level is reset and starts over again with the Level 1 reminder next time. Additionally, by pressing the button on the “ARYS™ me|tracker” once, the LED lights will show the percentage of the daily target that is already reached (one white LED = <25%; two white LEDs = 25–49%; three white LEDs = 50–75%; three white LEDs and one blinking LED = 75–99%; four white LEDs = 100%, daily target reached) and the patient receives vibration feedback. When the patient has reached the daily target, the tracker vibrates.

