**Secondary outcomes**					
MAL—14 (Quality of Movement)	Patient-reported quality of upper limb use in daily life	X		X	X
Fugl-Meyer Assessment—Upper Extremity	Upper limb motor function	X		X	X
Action Research Arm Test	Upper limb capacity	X		X	X
EuroQol Five Dimensions Five Levels Questionnaire	Health-related quality of life	X		X	X
Modified Rankin Scale	Global disability	X		X	X
Global Rating of Perceived Changes	Self-perceived change			X	X
Quantitative Sensor Data	Compliance; activity counts of the paretic and non-paretic side		X		
Adverse Events	Safety	X	X	X	X

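### The stated T0–T1 (and T1–T2) ANCOVA cannot be run for the sensor data, because no sensor value is scheduled at T0, T1 or T2 or before randomisation

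*Protocol article*

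**What the plan says.** The Statistical Analysis section of the protocol article sets one analysis for the primary outcome and a list of secondary outcomes. It opens with "Differences in change scores (T0–T1) between groups will be analyzed for the primary outcome (MAL—14 AOU" and continues with "secondary outcomes (MAL—14 QOM, FMA—UE, ARAT, EQ-5D-5L, mRS, and Quantitative Sensor Data". It adds "In addition, change will be monitored in the follow-up assessments (T1–T2" for follow-up, and the method is "An analysis of covariance will be applied, with the baseline value of the measure of interest as a covariate". No exception is made for the sensor data.

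The measurement plan treats the sensor data differently from the rest of that list:

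- **Table 1.** The sensor row ("Compliance; activity counts of the paretic and non-paretic side") has a single mark, in the intervention column. The other five secondary outcomes in the list are marked at T0, T1 and T2.
- **Stepwise Procedures.** "Randomization will take place after the baseline assessment and depending on the group allocation, participants will be handed over the trial arm-specific devices".
- **Experimental Intervention.** "The devices should be worn every day, as long as possible over a period of 6 weeks", and "During this 6-week period, a three-axis accelerometer in each device will constantly monitor the subjects’ arm movements". The device's daily goal starts from a preset value, so no run-in recording is described.
- **Secondary Outcomes, the sensor data subsection and the Discussion.** These place the sensor outcome inside the six intervention weeks: Arm Activities of each limb, their course over time, and the paretic limb against the non-paretic one. The Discussion expects the arms to differ in how these counts change.

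**The concern.** A change score needs a start and an end value, and the covariate needs a value from before randomisation. By the article's own schedule the trackers produce neither. This is not a detail left to a fuller document: the article states an analysis that its schedule contradicts.

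It matters because of what the sensor measures. The primary outcome is patient-reported, and participants in the experimental arm necessarily notice the feedback. FMA-UE and ARAT measure function and capacity, not what the arm does at home. The tracker counts are the only objective record of daily-life arm use. If the stated model cannot be run, its replacement will be chosen once the data exist. The candidates (first day, first week, slope, overall mean, last week) can give different answers.

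**Working it through.** The plan gives no figure for the sensor outcome. Its sample size concerns the primary outcome only and is not at issue: 2 × (1.96 + 0.84)² × 1.00² / 0.75² = 27.9, so 28 per group, as stated.

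**Step 1: what the model needs and what is scheduled.** The T0–T1 analysis regresses Y(T1) − Y(T0) on arm and Y(T0). The follow-up analysis uses Y(T2) − Y(T1).

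| Value | Role | Scheduled for the sensor data? |
|---|---|---|
| T0 | start of change; covariate | No. No mark in Table 1; devices are issued after baseline and randomisation |
| T1 | end of change; start of follow-up change | No. No mark; the visit is at day 45 ± 3, i.e. days 42 to 48, and wear lasts 6 × 7 = 42 days |
| T2 | end of follow-up change | No. No mark; the visit is at day 90 ± 6, i.e. days 84 to 96 |

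None of the three values is scheduled. Even if the last days of wear are allowed to stand for T1, T0 is still missing.

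**Step 2: why early wear is not a neutral replacement for T0.** The article does not propose this; the step shows what would follow. Let D be the true between-arm effect late in the six weeks, f the share of D already present in the early-wear value, and b the within-group slope of the late value on the early value. Both f and b are assumptions.

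- Change score: D − fD = (1 − f)D.
- ANCOVA: late difference minus b times early difference = D − b·fD = (1 − b·f)D. Using the change score or the late value as the outcome gives the same arm coefficient.

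| f | Change score | ANCOVA, b = 0.5 | ANCOVA, b = 0.9 |
|---|---|---|---|
| 0.25 | 75% | 87.5% | 77.5% |
| 0.50 | 50% | 75% | 55% |
| 0.75 | 25% | 62.5% | 32.5% |
| 1.00 | 0% | 50% | 10% |

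**Step 3: an effect that builds linearly.** Assume the effect on day t is t/42 of its day-42 size.

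- Week-1 mean: 3.5/42 = 1/12. Week-6 mean: 38.5/42 = 11/12, or 92%.
- Week 6 minus week 1: 10/12 = 83%.
- ANCOVA with week 1 as covariate: 11/12 − b/12, which is 87.5% at b = 0.5 and 84% at b = 0.9.
- Mean over all six weeks: 21/42 = 50%.

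The loss from using early wear is therefore large for an effect that starts early and small for one that builds slowly. A plain six-week average does the reverse: it keeps an immediate effect whole and halves a linear one. The replacement analysis has to allow for both.

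**The case against.** The strongest reply is that this is one over-inclusive list in a condensed article. The sections that define the sensor outcome place it within the six weeks, and a comparison of arms over that period is feasible. The outcome is secondary, the aims call this work exploratory, and the Discussion says that the trial is not powered for it. All of that stands, and it limits the severity. It does not remove the contradiction, because the only model stated for these data asks for values that are not collected.

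Four stronger readings are tempting, and the documents do not support them:

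- **That the sensor data cannot be analysed at all.** Only the stated ANCOVA fails; the data support a within-intervention comparison.
- **That the planned analysis is biased toward no effect.** Nothing in the article makes the first week a baseline. The attenuation in the working is a warning about a substitute. Nor would an immediate effect vanish whatever its size: that holds for an unadjusted change score, while ANCOVA keeps 1 − b of it.
- **That the sensor is the only outcome free of reporting bias.** FMA-UE and ARAT are performance tests scored by blinded assessors. The sensor is unique only as an objective measure of daily-life use.
- **That unequal wear time will distort the counts.** Counts do accrue only while a tracker is worn. But wear instructions and weekly calls are common to both arms, compliance is compared between them, and no difference is expected. The article gives no basis for an imbalance of any particular size. Scaling for wear belongs in a well-specified replacement; its absence here is not a separate error.

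**Conclusion.** The point holds as an internal contradiction. The T0–T1 and T1–T2 analyses assigned to the Quantitative Sensor Data need three visit values and a pre-randomisation covariate, and none of these is scheduled. This follows from the article's text and Table 1 alone, with no numerical assumption. The attenuation figures do rest on assumed f and b, and on a linear build-up where stated; they apply only if early wear were used as a baseline.

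The severity is moderate. The outcome is secondary and unpowered, and neither the primary MAL-14 AOU analysis nor the sample size is touched. A correction is still worth making before analysis, since this is the one objective measure of the behaviour that the device is meant to change.

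**What to change.** Take Quantitative Sensor Data out of the sentence that assigns T0–T1 and T1–T2 change by ANCOVA, and state a separate analysis for it:

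- Compare the arms on paretic-arm Arm Activities over the six intervention weeks, for example with weekly values in a repeated-measures model.
- Adjust for MAL-14 AOU at T0 and FMA-UE stratum, both of which are known before randomisation.
- Express activity per hour of wear or as the paretic/non-paretic ratio.
- Show the weekly course by arm and name in advance a late-period contrast beside any overall average.
- Say explicitly that early wear is not a baseline, because it follows randomisation and is under feedback in one arm.

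The cost is a change of wording and some extra processing of data already collected. There are two statistical costs. The comparison is less precise than one adjusted for a true sensor baseline. An average over all six weeks also dilutes an effect that builds gradually, to about 50% of its final size if the build-up is linear, which is why the late-period contrast is needed. A recording with feedback off before randomisation would supply a real baseline, but it needs a protocol amendment, and since recruitment began in September 2017 it would be missing for participants already enrolled.
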